### Randomization

Practices are the unit of randomization. Each of the 8 PCPs was randomly allocated to either the intervention arm (He Korowai Manaaki) or the control arm (usual care) of the trial. Covariate constrained randomization [11,12] was used to minimize potential imbalance between intervention and control arms in the size of the Māori population aged less than 1 year. Information on enrollment size and numbers of Māori patients aged less than 1 year was collected for each of the 8 participating PCPs. All possible allocations of these PCPs to the 2 trial arms were then enumerated using an algorithm blinded to the practice names. The list of allocations was then narrowed down to the ones that gave approximate balance in the numbers of Māori aged less than 1 year across the 2 arms, with each arm having 4 clusters (PCPs). Finally, the actual allocation was chosen randomly from this constrained list, thereby achieving an acceptable allocation while retaining randomness in the selection process. No practices dropped out of the study.

### Control Arm (Usual Care)

Women enrolled in control practices who are pregnant during the study period receive usual care and will be included as controls in the trial. In Aotearoa New Zealand, usual care means that a woman chooses their LMC, and for most women, their LMC is an independent or self-employed midwife [13]. A high proportion of the control cohort is likely to have engaged with primary care early in pregnancy but continued primary health care involvement during pregnancy and postpartum is unlikely. Usual care for the control cohort is expected to be predominantly midwifery-led pregnancy care.

### Intervention Arm (He Korowai Manaaki)

The He Korowai Manaaki intervention addresses both clinical care (pregnancy, postpartum, neonatal, and reproductive health) and the structural determinants of health (eg, housing, transport) with a best-practice pathway. He Korowai Manaaki includes responses to recommendations from the New Zealand Perinatal and Maternal Mortality Committee [14] and is in line with recommendations to address structural determinants of health by the Select Health Committee Inquiry into Improving Child Health Outcomes [15]. As a practice service change, He Korowai Manaaki is facilitated through primary care–held appointments including an extended first visit (First Touch), a follow-up visit, a third trimester visit, and a 6-week postnatal whānau (family) visit. Usual lead maternity care continues throughout.

General practitioners, nurse practitioners, and practice nurses at intervention PCPs were asked to attend an introductory training session on He Korowai Manaaki to enable the practice service change. The in-practice session provided by the researchers included education refreshers of evidence-based antenatal care, postnatal care, and contraception as well as information on the 4 study-funded appointments and utilization of the pregnancy wraparound care computerized advanced form installed into their practice management system. Education refresher sessions are provided by the researchers and associated experts over the course of the trial.

Clinicians in intervention PCPs work from the computerized advanced form to support care, screening, and navigation to allied services. This includes referrals to specialist care and services meeting the needs of wraparound care (eg, housing program, social work services, driving licensing programs, and dental practices).

Intervention practices are also supported to provide contraception of the woman’s choice, free of charge (see third trimester appointment and 6-week postnatal appointment in Textbox 1) and support with transport to pregnancy-related appointments (see First Touch appointment in Textbox 1).

Posters and published material on display at each intervention practice inform the enrolled population of the He Korowai Manaaki practice change taking place for the duration of the research project. All women identifying as pregnant in a primary care appointment are informed that their practice is offering an augmented pathway of care for pregnant women as part of the research project.

Information about the project is also shared with individual women by the general practitioner, nurse practitioner, or practice nurse. Each woman is asked to provide informed written consent for their deidentified outcome data (pregnancy and infant health information) to be shared with the research group in the future. The augmented pathway visits (Textbox 1) are explained, with the First Touch appointment then being offered to all women (with no data being shared for nonconsenting women). All women are then invited to attend the other study appointments (free of charge), and a recall for the next appointment is set.

There are no exclusions. The augmented pathway of care is available at any stage of pregnancy, for all pregnancies (low-risk and high-risk).

He Korowai Manaaki appointment descriptions.First Touch appointment **-** an extended first antenatal appointment that includes:Time taken to respond fully to concern and queriesOffer of screening for congenital abnormalities, sexually transmitted infections, family violence, and maternal mental health, with referrals as warrantedDiagnosis of any underlying medical conditions, with referral to secondary care as appropriateIdentification of risks (maternal age, obesity, maternal mental health problems, multiple pregnancy, socioeconomic deprivation, maternal medical conditions, previous preterm deliveries) with referral to secondary care as appropriateNavigation to lead maternity carer (LMC)Offer of prescribed pregnancy medications (folic acid, iodine)Whānau (family) checklist to assess whether support is required for transport to appointments, safe housing, finance, and oral health with connection offered to existing services and supportFollow-up appointment, including:Follow-up of tests that have been ordered, making sure all appropriate referrals have been madeEnsure enrollment with LMCAdministration of maternal vaccinations, when appropriateThird trimester appointment (open to woman’s midwife or whānau [family] to attend), including:Maternal vaccinations and planning for infant(s), including the provision of best-practice information about maternity health, child healthConversation about and planning for postnatal contraception6-week postnatal appointment (open to woman’s midwife or whānau [family] to attend), including:Addressing any concerns and answer queriesProvision of free contraceptiveScreening for infections, family violence, and maternal mental health, with referrals as appropriateEducation around nutrition, smoking, alcohol use, and drug useEducation around pelvic health, navigation to women’s physio service as appropriateNavigation to oral health care servicesNavigation to support services such as Family Start, Well Child/Tamariki Ora, and Early Childhood Education services

### Primary Outcome Measures

The primary outcome is the increase in timely vaccinations for Māori infants. Timely vaccination is defined as all age-appropriate vaccinations completed by 6 months of age.

### Secondary Outcome Measures

Secondary outcomes include infant hospitalizations and length of stay until 1 year of age as well as obstetric, delivery, and infant outcomes plus service engagement outcomes (contraception, oral health, WCTO, Early Childhood Education [ECE]; see Table 1).

**Table 1 table1:** Outcome variables and data sources.

Data source	Data source description	Examples of outcome variables
ELI^a^	The Ministry of Education information system for Early Childhood Education (ECE) collects information on participating children's enrollment and attendance.	Infant registration with ECE/Te Kōhanga Reo at 2 years of age^b^
MAT^c^	The MAT provides statistical, demographic, and clinical information about selected publicly funded maternity services up to 9 months before and 3 months after a birth. It also contains inpatient and day-patient health event data on pregnancy, birth, and the postnatal period for mother and baby, sourced from the National Minimum Dataset (administered by the MOH^d^).	Maternal ethnicity; smoking status at time of booking with a maternity care provider and at 2 weeks postdelivery^b^; hospitalization episodes^b^; antenatal screening^b^; plurality; parity; mode of delivery^b^; Apgar scores^b^; birthweight; gestational age at delivery^b^; infant hospitalization in first year of life^b^; breastfeeding status at infant discharge^b^, 2 weeks^b^, and 6 weeks
MOH	The MOH receives data from different parts of the health sector through the utilization of health services or mandatory reporting national collections and also from national population health surveys.	Infant registration to oral health services at 2 years of age^b^
MORT^e^	The MORT classifies the underlying cause of death for all deaths registered in New Zealand and all registerable stillbirths using the World Health Organization Rules and Guidelines for Mortality Coding.	Infant mortality^b^, ethnicity, date of death, gestational age at death, birthweight, diagnostic codes on cause of death, sudden and unexpected death indicator
NIR^f^	The NIR is a computerized information system that has been developed to hold immunization details of New Zealand children (administered by the MOH).	Infant vaccination at 6 weeks^g^, 3 months^g^, 5 months^g^, and 15 months^b^
NHI^h^	The NHI is a system used by public hospitals and other health and disability support services to assign an alphanumeric identifier (the NHI number) to people who use their services.	NHI number, area deprivation, ethnicity (maternal and infant)
NMDS^i^	The NMDS is a national collection of public and private hospital discharge information, including coded clinical data for inpatients and day patients (hospital events).	Ethnicity; diagnostic codes (ICD-10^j^)^b^; maternal, antenatal, or postnatal hospital admissions (public)^b^; discharge dates and length of stay; infant hospital admissions (public)^b^; discharge dates and length of stay
PHO^k^	The PHO provides a national enrollment collection that holds patient enrollment data.	Infant engagement with general practitioner <8 weeks postdelivery or after infant discharge from hospital^b^
WCTO^l^	The WCTO program is a series of health assessments and support services for children and their families from birth to 5 years and is a gateway for parents to access primary and specialist health care, education, and social services. WCTO providers submit service coverage and data to the MOH.	Attendance at scheduled WCTO infant appointments at 8-10 weeks^b^, 3-4 months^b^, 5-7 months^b^, 9-12 months^b^, and 15-18 months^b^; breastfeeding status at 3 months and 6 months^b^

^a^ELI: Early Learning Information System – Ministry of Education.

^b^Secondary outcome.

^c^MAT: National Maternity Collection.

^d^MOH: Ministry of Health.

^e^MORT: Mortality Collection.

^f^NIR: National Immunisation Register.

^g^Primary outcome.

^h^NHI: National Health Index.

^i^NMDS: National Minimum Dataset.

^j^ICD-10: International Classification of Diseases, Tenth Revision.

^k^PHO: Primary Health Organisation.

^l^WCTO: Well Child/Tamariki Ora.

### Data Collection

The data for our study are generated from national and local information collections, as described by Filoche et al [16]. In Aotearoa New Zealand, the Ministry of Health (MOH) is responsible for the oversight and funding of the country’s 20 district health boards. Select clinical information is routinely reported by each health board to the MOH and is collated into national datasets with operational responsibility by the Client Insights and Analytics group. Outcome data will be collected using Aotearoa New Zealand’s unique patient National Health Index (NHI) number to source clinical and demographic data from multiple national datasets (Table 1).

At study end, intervention practices will send the NHIs of women who have provided consent for their deidentified outcome data to be collected and analyzed (linked to the NHI of an infant) to the MOH. The MOH will also receive from each control practice the NHIs of women registered with them during the study’s recruitment period. To identify the control group (women enrolled with PCPs, pregnant during the study period) and the associated linked infant(s) following the relevant designated time period (Figure 1), the MOH will match the NHIs provided by the control practices to national datasets containing maternity, pregnancy, and delivery information (eg, the National Maternity Collection and the National Minimum Dataset).

**Figure 1 figure1:**
[figure not shown]
He Korowai Manaaki (HKM) timeline. MOH: Ministry of Health; NHI: National Health Index.

### Study Variables

Primary and secondary outcomes will be tracked by patient NHI without names. The NHIs will be matched to multiple national databases (Table 1) up until the infant is 2 years of age to source clinical and demographic data to provide a combined data source for (1) sociodemographic information (ethnicity, New Zealand Index of Deprivation [socioeconomic status], maternal age), (2) clinical information (parity, plurality, LMC, gestational age at booking), (3) obstetric outcomes (gestation at delivery, cesarean section, Apgars, mortality, and morbidity), (4) antenatal screening (LMC registrations), (5) smoking status (maternal smoking status at booking and after delivery), (6) vaccination status (timely access to age-appropriate immunizations), (7) infant hospitalizations (cause of mortality, intraventricular hemorrhage [bleed in brain], oxygen required on discharge, and length of stay in neonatal intensive care unit), (8) access to child health services (number of oral health or WCTO visits, general practice registrations), and (9) access to ECE (ECE registrations).

### Analysis

Data analysis will occur as soon as outcome data are available for the intervention and control arms. Within a Kaupapa Māori inquiry paradigm [8-10], the primary analysis is for Māori, with secondary analysis for non-Māori [17]. An intention-to-treat analysis will be undertaken [18] using individual participant data. All pregnancies will be analyzed (regardless of the number of He Korowai Manaaki appointments attended), with the primary cohort being women seen in a PCP before 20 weeks of pregnancy.

The rate of infant hospitalizations will be analyzed using Poisson regression, and if there is evidence of overdispersion or underdispersion, then negative binomial model will be used. A generalized linear mixed model with a logit link will be used to analyze binary outcomes, and a linear mixed model will be used to analyze continuous outcomes. All regression models will adjust for potential personal and care-related confounders and for the effect of clustering within practices. Sensitivity analyses will be undertaken for the primary outcome to determine the impact of missing data, and per protocol analyses will be conducted. The consistency of effects for prespecified subgroups will be assessed using tests for heterogeneity.

Descriptions of rates, rate ratios, odds ratios, and respective 95% confidence intervals will be reported. Results will be aggregated, and no individual practice will be identifiable.

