### Sample Size

A total of 8 practices and 216 Maori participants (4 practices and 108 Maori participants in each group) will provide 80% power at a two-sided α of .05 to detect an 18.5% difference in the proportion of infants who receive all age-appropriate vaccinations by 6 months of age between the groups. For these figures, we have assumed an average cluster size of 27, intracluster correlation coefficient of 0.01, and that 83.5% of the infants will receive all age-appropriate vaccinations by 6 months of age in the intervention group and 65% in the control group. Our total sample size requires 432 pregnancies (216 control, 216 intervention).

Based on the expected recruitment rate and pregnant women meeting the entry criteria for the core intervention (ie, seen in a PCP before 20 weeks of pregnancy), He Korowai Manaaki is offered through intervention practices to all pregnant women for approximately 18 months from the commencement of the study to obtain the required sample size.

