## Results

This cluster randomized clinical trial is underway with 8 PCPs. Practices have been randomized to either the intervention arm or control arm. Recruitment of women ended in June 2020, with 293 women enrolled in the intervention arm, of which 251 women (the primary cohort) were seen in a PCP before 20 weeks of pregnancy. Data collection will commence in early 2022 and be complete by mid-2023, and the analysis results are anticipated to be published in late 2023. The explicit and conscious decision to use an indigenous lens when analyzing the data allows outcomes to be viewed with a focus on advantage and privilege rather than one of disparity.

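### The primary cohort is defined by early attendance after randomization, is counted only in the intervention arm, and has no stated counterpart among controls

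*Protocol article*

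**What the plan says.** The Analysis section contains two statements about who is analyzed. One is intention-to-treat: "All pregnancies will be analyzed (regardless of the number of He Korowai Manaaki appointments attended"). The other narrows it, "with the primary cohort being women seen in a PCP before 20 weeks of pregnancy". The Sample Size section shows where the 20-week condition comes from: it refers to "pregnant women meeting the entry criteria for the core intervention (ie, seen in a PCP before 20 weeks of pregnancy"). The condition is therefore an entry criterion for the intervention.

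The Results section reports the cohort in one arm: "293 women enrolled in the intervention arm, of which 251 women (the primary cohort) were seen in a PCP before 20 weeks". No control figure is given.

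For controls, the Control Arm section says: "Women enrolled in control practices who are pregnant during the study period receive usual care and will be included as controls in the trial". It adds only an expectation that many of them will have had early contact with primary care. Under Data Collection, control practices supply the identifiers of registered women, and "the MOH will match the NHIs provided by the control practices to national datasets containing maternity, pregnancy, and delivery information". The one primary-care source in Table 1 is an enrollment register: "The PHO provides a national enrollment collection that holds patient enrollment data".

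**The concern.** Practices were randomized, not women. Whether a woman is seen at her practice before 20 weeks is decided after allocation. In intervention practices, posters advertise the pathway to enrolled women and the study visits are free, so allocation may change who presents early. A cohort selected on that event is not the intention-to-treat population that the same paragraph promises and that the Limitations section relies on.

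The second difficulty is measurement. The rule needs the date of a mother's visit to her practice. Intervention practices know it. For controls, the described data flow yields registration, maternity, hospital, immunization and child-service records, none of them described as holding that date. If the text is followed, women seen late leave the intervention arm while comparable women stay among the controls. If late-seen women's infants are vaccinated on time less often, part of any observed benefit would come from the choice of population and not from the pathway.

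**Working it through.** **1. The plan's own sample size.** Inputs (Sample Size section): 65% versus 83.5%, two-sided 5%, 80% power, cluster size 27, intracluster correlation 0.01.

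- Design effect = 1 + (27 − 1) × 0.01 = 1.26.
- Pooled-variance formula: 87 × 1.26 = 109.6 per arm. Unpooled: 83.8 × 1.26 = 105.5.
- Power at 108 per arm: 79.6% (pooled) or 80.9% (unpooled).

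The stated 108 per arm reproduces, so that arithmetic is not in question here.

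**2. What the 20-week rule removes.** Intervention arm (Results): 293 − 251 = 42, and 42/293 = 14.3%. Control arm: not computable from the document.

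**3. The rule beside the control data.**

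| Element | Intervention | Control |
|---|---|---|
| Who enters | Women seen in the practice who consent | Women enrolled in the practice and pregnant in the study period |
| 20-week visit condition | Applied: 251 of 293 | None stated |
| Source for visit date | Practice | None described |
| Nearest timing variable | Gestational age at booking (Study Variables) | Same |

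Gestational age at booking is listed next to the lead maternity carer. It is at most a proxy for a practice visit, and the article does not give it this role.

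**4. Possible size.** Assume no true effect, 65% coverage overall in both arms, the same late-seen share f = 0.143 in both arms, and trimming in the intervention arm only. Let d be the coverage gap between early-seen and late-seen women's infants (assumed; the document gives none). From (1 − f) × early + f × late = 0.65 and early − late = d:

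- early = 0.65 + f × d, so the spurious difference is f × d.

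For the type I error, take 108/1.26 = 85.7 effective infants per arm. The standard error is √[(early × (1 − early) + 0.65 × 0.35)/85.7], with a two-sided normal test.

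| Assumed gap d (points) | Spurious difference (points) | Approximate two-sided type I error |
|---|---|---|
| 5 | 0.7 | 5.1% |
| 10 | 1.4 | 5.5% |
| 15 | 2.15 | 6.0% |
| 20 | 2.9 | 6.8% |
| 30 | 4.3 | 9.2% |

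At d = 15, for example: 0.1433 × 15 = 2.15 points; the standard error is 0.0723; the shift is 0.0215/0.0723 = 0.30 standard errors.

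Two limits apply. The 42 and 293 are women of all ethnicities, while the primary analysis is for Māori, and no late-seen share for Māori is given. The normal approximation also ignores the small number of practices.

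**The case against.** The strongest reply is that the Analysis section words the rule without reference to arm, so it may be meant for both. Table 1 gives only examples of outcome variables, Data Collection mentions local as well as national collections, and booking gestation is among the study variables. A control-side rule may exist in the full protocol. This stands to a degree: a reader might infer that the criterion cannot be observed in controls and removes none of them, but the article does not say so. What it does do is fix a primary cohort, count it in one arm, and state a control inclusion rule without the condition. That goes beyond omitted detail. Applying the rule in both arms would still select on an event that allocation can influence.

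It can also be said that all pregnancies will be analyzed and that models adjust for care-related confounders. The first is the statement that conflicts with the primary cohort. The second cannot remove a difference in early attendance if attendance is not measured in controls.

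Two larger claims are tempting. One is that many controls were already past 20 weeks when recruitment opened and so have no intervention counterpart. That rests on a literal reading of the control rule, whereas Data Collection ties the control period to Figure 1, which is not available here. The other is to enlarge the bias by counting women who never attend. They are missing from the intervention data because only women who were seen and consented contribute (Design, Intervention Arm, Data Collection), which is a separate matter from the 20-week rule.

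**Conclusion.** The point holds in this form: the article states two analysis populations that are not the same, and the one named primary depends on attendance after randomization, is reported for one arm, and has no described means of being applied to the other.

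A reader might go further and conclude that the primary result is biased towards benefit. The document does not support that. It gives no link between early attendance and vaccination, and its expectation that a high proportion of controls engaged early would, if right, shrink any bias. Under the assumptions shown, the spurious difference is about 0.7 to 4.3 points, against a target of 18.5; the sign would reverse if late-seen women's infants had higher coverage. The weight of the point lies less in that size than in the lack of a common population, which makes a positive result harder to attribute to the pathway. It should be fixed; confidence is medium, because a control-side rule may exist in documents not shown.

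**What to change.** Define one primary population that is computed the same way in both arms and does not depend on attending the practice. One workable rule is all pregnancies below 20 weeks' gestation on at least one day of the recruitment period, derived from delivery date and gestational age at delivery; the latter is already listed under the National Maternity Collection in Table 1. Move the early-attender cohort to a secondary analysis. Reconcile the Sample Size, Control Arm, Data Collection, Analysis and Results sections with that definition.

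The cost is a wording change and one derived variable. The article has data collection starting in early 2022, so at its publication in January 2021 the change could still be made before outcomes were seen. The downside is some dilution from late-seen women: at most 42 of 293 enrolled intervention women (14.3%) return to the primary population, fewer if some had already passed 20 weeks when recruitment opened.

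The rule removes the 20-week asymmetry only. Intervention data will still come from women who were seen and individually consented, while control data are taken without consent. That filter should be acknowledged when the result is interpreted.

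### The negative binomial fallback for infant hospitalizations cannot represent underdispersion, so one of the two branches of the switching rule does nothing

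*Protocol article*

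**What the plan says.** The Analysis section of the protocol article names Poisson regression as the first model for this count outcome. Its switching rule reads: "if there is evidence of overdispersion or underdispersion, then negative binomial model will be used". The same fallback therefore serves both directions of departure from the Poisson variance.

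The outcome is a secondary one. The section on secondary outcome measures states: "Secondary outcomes include infant hospitalizations and length of stay until 1 year of age".

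Two further sentences in the Analysis section apply. On adjustment: "All regression models will adjust for potential personal and care-related confounders and for the effect of clustering within practices". On reporting: "Descriptions of rates, rate ratios, odds ratios, and respective 95% confidence intervals will be reported". No other method for dispersion is named in the article, and the clustering adjustment is not presented as a remedy for underdispersion.

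**The concern.** A fallback model is useful only if it can represent the departure that triggers it. The negative binomial adds variance to the Poisson and cannot remove any. If the hospitalization counts varied less than a Poisson model implies, the rule would send the analyst to a model whose best fit is the one just set aside, or which does not converge at its boundary.

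Two things are at stake, both limited. The model-based interval for the hospitalization rate ratio would be wider than it need be. And the analyst would have to improvise another method after seeing the outcome data, which prespecifying a rule is meant to avoid.

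**Working it through.** The article gives no hospitalization rate and no dispersion figure, so there is no stated number to reproduce. The check has an algebraic part, which needs no assumption about the data, and an illustration, which does.

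**1. Variance of the two models.** Poisson: Var = μ. Negative binomial: Var = μ + αμ², α ≥ 0. Dividing by μ, the negative binomial variance-to-mean ratio is 1 + αμ. At μ = 0.5:

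| α | Var | Var/mean |
|---|---|---|
| 0 | 0.500 | 1.00 |
| 0.1 | 0.525 | 1.05 |
| 0.5 | 0.625 | 1.25 |
| 1 | 0.750 | 1.50 |

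The ratio is never below 1, whatever the mean or the sample size.

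**2. Size of the effect if the branch arose.** If the true ratio is φ < 1 and infants are independent, a model-based Poisson standard error (SE) is too large by the factor 1/√φ:

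- φ = 0.75: 1/√0.75 = 1.155, about 15% too wide.
- φ = 0.70: 1/√0.70 = 1.195, about 20% too wide.

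Both values of φ are assumptions. For whole-number counts with mean μ ≤ 1 the smallest possible variance is μ(1 − μ), so φ ≥ 1 − μ. A ratio of 0.75 therefore needs a mean of at least 0.25 admissions per infant, and 0.70 needs at least 0.30.

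**3. Simulation.** From the Sample Size section: 108 Māori participants per arm. Assumed: mean 0.5 admissions per infant, no treatment effect, no clustering, 1000 datasets per scenario. Underdispersed counts were drawn as Binomial(2, 0.25), with mean 0.5, variance 2 × 0.25 × 0.75 = 0.375 and ratio 0.375/0.5 = 0.75. Overdispersed counts were negative binomial with α = 1, ratio 1.5. True SE means the spread of the estimated log rate ratios across datasets.

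| Data | True SE | Poisson SE (type I error) | Negative binomial SE (type I error) | Quasi-Poisson SE (type I error) |
|---|---|---|---|---|
| Underdispersed | 0.169 | 0.194 (0.022) | 0.194 (0.022) | 0.168 (0.047) |
| Overdispersed | 0.236 | 0.195 (0.106) | 0.236 (0.055) | 0.237 (0.047) |

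In the underdispersed case α was estimated at 0 in all 1000 datasets, so the switch changed nothing: 0.194/0.169 = 1.15, in line with step 2. In the overdispersed case the switch did what it should.

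**4. Effect of clustering.** Assume 108 infants and 4 practices per arm, mean 0.5, φ = 0.7 and a between-practice SD of 0.15 on the log scale. Per arm:

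- Poisson part: 1/(108 × 0.5) = 0.0185.
- True within-practice part: 0.7 × 0.0185 = 0.0130.
- Between-practice part: 0.15²/4 = 0.0056.
- SE ratio: √[(0.0185 + 0.0056)/(0.0130 + 0.0056)] = 1.14, against 1.20 without clustering.

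**The case against.** The strongest reply is that the branch will probably never be used. Differences between infants that the model does not capture, and repeat admissions of the same infant, push hospitalization counts towards overdispersion, and there the rule works. If underdispersion did occur, the error would run in the safe direction: type I error 0.022 in the simulation, not above 0.05. This stands, and it limits the importance of the point.

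A second reply is that the clustering method for the count model is not stated. A robust-variance approach would not rely on the Poisson variance, so its intervals need not be too wide. This also stands, and it is why the conclusion is confined to model-based intervals. Even then the switch to the negative binomial would contribute nothing.

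A third reply is that a journal article leaves detail to the full analysis plan. That does not meet the point. The article does not leave the underdispersion method open; it names one that cannot work. A plan that followed the sentence would inherit the error, and one that departed from it would disagree with the published protocol.

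A reader might go further and object to choosing the model after a dispersion check at all. Prespecified checks of this kind are common practice and nothing in the article shows harm from this one, so that is not part of the point. Nor are an offset for follow-up time or a correction for the small number of practices. These are separate matters that the defect does not raise.

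**Conclusion.** The rule is wrong as written in one of its two branches. That follows from the variance formula alone and rests on no assumption about the data. In that branch the fit collapses to Poisson or fails to converge, and model-based intervals for the hospitalization rate ratio stay too wide.

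The consequence is minor. It concerns one secondary outcome, the branch is the less likely one, and the error is conservative. The figures of about 15% and 20% are illustrations that rest on assumed variance-to-mean ratios and independent infants; under the clustering assumptions above, 20% falls to about 14%.

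A reader might infer that the hospitalization analysis as a whole is unsound, that false-positive findings are likely, or that the main result is in doubt. The article supports none of these. The overdispersion half is sound, the shown error lowers type I error, and timely vaccination is a binary outcome analysed with a logit mixed model to which this rule does not apply.

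**What to change.** Change the one sentence in the Analysis section, and the matching sentence in the analysis plan if it repeats it. Limit the negative binomial switch to overdispersion. For underdispersion, name one method that allows dispersion below 1: quasi-Poisson with the scale estimated from the data, generalized Poisson or Conway-Maxwell-Poisson. Keep the stated adjustment for clustering within practices in whichever model is used, because an estimated scale does not by itself account for practices.

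The cost is one sentence. It needs no new data and no change to the design or sample size, and it can be settled before the outcome data are analysed.
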